### Sham group

The sham group will receive abdominal functional electrical stimulation via the VentFree device exactly as described above but with the sham stimulation amplitude determined at the eligibility screening. This amplitude is specifically designed to not cause an active muscle contraction.

### Criteria for discontinuing or modifying allocated interventions

Criteria for discontinuing or modifying allocated interventions are shown in table 1.

**Table 1 T1:** Criteria for discontinuing or modifying allocated interventions

The active or sham treatment must not be initiated if any of the following conditions are met:	Initiated treatment sessions must be paused if any of the following conditions are met:
Heart rate <50 beats per minute or >130 beats per minute	Heart rate <50 beats per minute or >130 beats per minute
Mean arterial pressure <60 mm Hg or >110 mm Hg (with or w/o vasopressors)	Mean arterial pressure <60 mm Hg or >110 mm Hg (with or w/o vasopressors)
Respiratory rate >35 breaths per minute	Respiratory rate >35 breaths per minute
SpO_2_ <90% (with ventilator support, O_2_ supplementation)	SpO_2_ <90% (with ventilator support, O_2_ supplementation)
BPS >4 or CPOT >2	Participant experiences a seizure
Participant refuses initiation of treatment	Participant requests to stop
	Increase in heart rate >20 beats per minute
	Increase in systolic blood pressure >20 mm Hg

BPS, Behavioural Pain Scale; CPOT, Critical-Care Pain Observation Tool; O2, Oxygen; SpO2, Peripheral Oxygen Saturation.

If a participant experiences a seizure during a treatment session, the session must be ended. If any of the other above-mentioned criteria are met causing the treatment to be paused, the participant should be re-evaluated every 2 min up to a maximum of 10 minutes to determine if their conditions have stabilised to within the stopping criteria parameters. If at any time during the 10-minute re-evaluation period, the participant’s parameters have returned to be within the above-mentioned criteria, the treatment can be resumed.

Participation in the trial is strictly voluntary. A participant, or their LAR, has the right to withdraw from treatment or the study at any time for any reason. The investigator also has the right to terminate the treatment or participation of a participant due to transfer to another institution, significant adverse events, any other reason relating to the participant’s safety or integrity of the trial data, participant non-compliance with the study assessments or procedures, or any problem deemed by the investigator to be sufficient to cause discontinuation from treatment or study participation. The site PI will inform the participant of the withdrawal.

### Strategies to improve adherence to interventions

Stimulation parameters are titrated to avoid participant discomfort at every treatment session. We believe this is an effective way to improve adherence in this trial. Furthermore, after the first week, stimulation is only applied on 5 of 7 days to hopefully improve adherence.

### Relevant concomitant care permitted or prohibited during the trial

All participants will continue to receive standard of care throughout the trial. There will be no limitations placed on the care a participant can receive during the trial. To reduce variability in mechanical ventilation weaning practices, all sites will use a standardised weaning protocol (online supplemental appendix B).

### Provisions for post-trial care

Participants will not receive the intervention beyond day 28 or ICU discharge, whichever comes first. All sites, and the trial sponsor, have appropriate insurance provisions in place to ensure protection of all participants.

### Outcomes

#### Primary outcome

The primary outcome is time (in days) from first administration of the VentFree intervention to successful liberation from mechanical ventilation, defined as disconnection from mechanical ventilation that does not require invasive mechanical ventilation in the subsequent 7 days after disconnection,^33^ or until ICU discharge (as defined above), or until live hospital discharge, whichever occurs first.

#### Secondary outcomes

Key secondary outcomes are CPF (minimum 24 hours post-extubation once the patient meets awakening criteria^13 34^) and MEP (minimum 24 hours post-extubation once the patient meets awakening criteria^13 34^). The best (maximum value) of three attempts will be used in the analyses of each individual parameter.^34^ The full pulmonary function testing protocol is provided in online supplemental appendix C.

Other secondary outcomes are:

Incidence of device-related adverse events (hospital discharge).Time from first administration of the VentFree intervention to ICU discharge.Time from first administration of the VentFree intervention to hospital discharge.Incidence of successful liberation from mechanical ventilation (day 28 or ICU discharge, whichever comes first).Incidence of reintubations (ICU discharge, 90 days post treatment).Incidence of readmissions to the ICU (90 days post treatment).Incidence of readmissions to the hospital (90 days post treatment).Incidence of acute respiratory infections (hospital discharge).Incidence of hospital-acquired infections (hospital discharge).Incidence of tracheostomy (ICU discharge).Mortality (hospital discharge, 90 days post treatment).Maximum inspiratory pressure (minimum 24 hours post extubation once the patient meets awakening criteria).Mobility as assessed by the ICU Mobility Scale^35^ (ICU discharge).Quality of life as assessed by the 5-level EQ-5D version (EQ-5D-5L)^36^ (90 days post treatment).

The full schedule of assessments is shown in the participant timeline in figure 2.

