**Methods and analysis:**

This pivotal superiority trial will be performed in up to 30 intensive care units (ICUs) in the USA, France, the Netherlands and Australia. Adults (≥22 years old) who have been mechanically ventilated for 24–96 hours and are expected to remain ventilated for another 24+ hours are potentially eligible. We will recruit participants until 150 successful liberations from mechanical ventilation occur. To achieve this, we estimate that a maximum of 272 participants will be randomised in a 1:1 ratio to receive 30 min of active exhalation synchronised abdominal functional electrical stimulation (vs sham). The intervention will be applied using the VentFree Respiratory Muscle Stimulator two times per day, a minimum of 5 days per week, for a maximum of 28 days or until ICU discharge. The primary outcome is time from first intervention to successful liberation from mechanical ventilation. Secondary outcomes include cough peak flow (CPF) and maximum expiratory pressure (MEP) at 24 hours post-extubation, hospital and ICU length of stay, reintubations, complications, ICU readmissions, 90-day mortality and quality of life. The participant, clinical team and outcome assessor are blinded to group allocation. A positive outcome has the potential to improve patient-centred outcomes in ICUs.

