Neuromuscular electrical stimulation, the application of small electrical pulses to the motor nerves supplying a muscle to elicit a contraction, has been shown to be a safe and effective technique to reduce muscle atrophy and critical illness polyneuromyopathy in critically ill patients.^25^ When neuromuscular electrical stimulation is applied to the abdominal wall muscles in synchrony with exhalation, termed abdominal functional electrical stimulation, the effect on ventilation is similar to a physiological contraction of the abdominal wall muscles. Previous studies have shown that abdominal functional electrical stimulation can acutely improve respiratory function^26^ and increase tidal volume and reduce duration of mechanical ventilation for people with tetraplegia.^27^ Importantly, abdominal functional electrical stimulation does not require patient cooperation.

We completed two pilot clinical trials that examined abdominal functional electrical stimulation using the VentFree device during invasive mechanical ventilation in critically ill patients.^28 29^ Both studies demonstrated the feasibility of applying this technology with critically ill mechanically ventilated patients. Notably, median ventilation duration and ICU length of stay were 10 versus 52 days (p=0.07) and 12 versus 54 days (p=0.03) for the intervention versus sham group, respectively. No serious device-related adverse events occurred, and treatment session compliance was >90%.^30^

The primary objective of the Pivotal Evaluation of Abdominal Functional Electrical Stimulation using the VentFree device for Weaning from Mechanical Ventilation (PREVENT) trial is to determine whether using the VentFree device reduces the time from first treatment to successful liberation from mechanical ventilation in critically ill adult patients.

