### Interventions

Participants will be randomly assigned to receive active stimulation delivered using the VentFree device or sham.

VentFree is composed of a control unit, breathing sensors (ventilator circuit flow sensor and nasal-oral cannula), disposable transcutaneous stimulation electrodes and a power supply. The ventilator circuit flow sensor, which is placed between the ventilator tubing and the participant interface (eg, endotracheal tube), is used for all patients who are endotracheally intubated, have a tracheostomy or are receiving non-invasive ventilation. For those liberated from mechanical ventilation, the nasal-oral cannula serves as a flow sensor—which is placed with the nasal prongs inserted in the participant’s nares and the oral prong suspended over their mouth. The nasal-oral cannula can be used together with either a high-flow or conventional oxygen cannula and can be used with most brands of high flow nasal cannula. Using the breathing sensor, the control unit monitors the breathing pattern of the participant to apply functional electrical stimulation in synchrony with exhalation. Figure 1 illustrates VentFree setup when using the ventilator circuit flow sensor. The stimulation electrodes and ventilator circuit flow sensor are replaced every 5 days of treatment and for every treated participant. The nasal-oral cannula is replaced after every treatment session.

All participants will receive 30 min of the VentFree intervention (or sham) twice per day, for a minimum of 5 days per week, for 28 days or until ICU discharge, whichever comes first.

Discharge from the ICU will be defined as the initial occurrence of any of the following:

Transfer order to a general or surgical floor team; orTransfer to a general or surgical floor; orDischarge from the ICU to an outside facility or home.

The first intervention session must be initiated ≤2 hours after randomisation, and a minimum of 4 hours is required between treatment sessions. Training will be provided by the sponsor for all trial procedures.

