### Follow-up visit

A follow-up visit is required 90 days (± 14 days) from the date of the final study treatment. The visit may be conducted in clinic or by phone or videoconference. The visit will record EQ-5D-5L,^36^ new hospitalisations, new intubations and mortality. If any participant’s score is 4 (severe) or 5 (extreme) in any section of the EQ-5D-5L, the research staff will notify the PI and instruct the participant to follow up with their primary care physician for further instructions.

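### 90-day mortality is counted from the last treatment, a date the device is meant to bring forward, so an effective device slightly shortens its own mortality window

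*Protocol article*

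**What the plan says.** Under Secondary outcomes, the protocol article lists "Mortality (hospital discharge, 90 days post treatment" as one of the other secondary outcomes. The Follow-up visit section places the visit at 90 days, give or take 14, counted "from the date of the final study treatment", and mortality is recorded there. Interventions sets the treatment period: twice-daily sessions "for 28 days or until ICU discharge, whichever comes first". Provisions for post-trial care repeats that limit. Time to ICU discharge is itself a secondary outcome. The abstract shortens the outcome to "90-day mortality and quality of life" and names no starting point.

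Reintubation and readmission use the same clock: "Incidence of reintubations (ICU discharge, 90 days post treatment", "Incidence of readmissions to the ICU (90 days post treatment" and "Incidence of readmissions to the hospital (90 days post treatment". None of these outcomes is in the fixed testing sequence, which covers the primary outcome, cough peak flow and maximum expiratory pressure.

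**The concern.** A comparison of cumulative mortality between randomised arms needs the same length of observation from randomisation in each arm. Here the end of observation is the end of treatment plus 90 days, and the end of treatment is largely set by ICU discharge. If the device works as hoped, active participants leave the ICU sooner, stop treatment sooner and reach the end of their mortality window sooner. Deaths that fall just after that point are missed in the active arm, while deaths on the same day after randomisation still count in sham.

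Early stopping of treatment, which the protocol allows, moves the clock in the same way. A participant who is randomised but never treated has no final treatment date at all. The article foresees such participants and gives them a day-1 rule for the primary outcome only.

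At stake is the credibility of the mortality result. Readers will look at it closely in ventilated ICU patients, and many will take 90-day mortality to mean 90 days from randomisation. Even a small built-in advantage for the device weakens any reassurance about deaths.

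**Working it through.** **The plan's own figure.** No figure is given for the 90-day outcomes. The sample size reproduces: events = 4(1.960 + 1.282)² / (ln 1.7)² = 149.3, rounded up to 150, and 150 / 0.55 = 272.7, against approximately 272 stated. The 90-day clock does not enter this calculation.

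**Range of the window.** The first session is due within 2 hours of randomisation, so randomisation and first treatment are nearly the same day. Window from randomisation = min(28, day of ICU discharge) + 90. It runs from about 90 days (treatment ends almost at once) to 28 + 90 = 118 days.

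**Extreme scenario: pilot medians.** The Introduction gives median ICU stays of "12 versus 54 days (p=0.03" for active versus sham. It does not say where the stay is counted from; I treat it as counted from first treatment and apply the medians to every patient.

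- Active: 12 + 90 = 102 days. Sham: 28 (the cap) + 90 = 118 days. The gap is 16 days.
- With one constant death hazard h in both arms, the spurious difference is exp(−102h) − exp(−118h).

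| Assumed h per day | Points lower in active |
|---|---|
| 0.05% | 0.76 |
| 0.1% | 1.43 |
| 0.2% | 2.57 |
| 0.3% | 3.45 |

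**Scenario at the design effect.** This was simulated with 1,000,000 participants per arm. The following inputs are assumptions and are not in the documents: exponential time to liberation with a sham hazard of 0.03 to 0.08 per day, ICU discharge 2 days after liberation, and a death hazard of 1% per day to day 28 and 0.1% or 0.3% per day afterwards, the same in both arms. The design value of 1.7, a subdistribution hazard ratio in the plan, was applied to the liberation hazard.

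| Sham liberation hazard | Late death hazard | Mean window, sham / active (days) | Active minus sham, current clock | Active minus sham, day 90 from randomisation |
|---|---|---|---|---|
| 0.03 | 0.1% | 107.8 / 104.8 | −0.23 | +0.02 |
| 0.03 | 0.3% | 107.8 / 104.8 | −0.61 | +0.02 |
| 0.05 | 0.1% | 104.9 / 101.4 | −0.22 | +0.06 |
| 0.05 | 0.3% | 104.9 / 101.4 | −0.70 | −0.01 |
| 0.08 | 0.1% | 101.8 / 98.5 | −0.11 | +0.15 |
| 0.08 | 0.3% | 101.8 / 98.5 | −0.69 | −0.01 |

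Differences are in percentage points, with simulation noise of up to about 0.15. The mean window is 3.0 to 3.4 days shorter in active. As a check, mean gap × hazard × share still alive gives 3.3 × 0.001 × 0.70 = 0.23 points and 3.3 × 0.003 × 0.60 = 0.59 points. At 0.05% per day, which was not simulated, it gives 3.3 × 0.0005 × 0.70 = 0.12 points. The range is therefore about 0.1 to 0.7 points, and a fixed day 90 removes it.

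**Reintubation and readmission.** These can occur only after liberation or discharge, so the relevant quantity is time at risk after that event. The pilot medians are 10 v 52 days for ventilation and 12 v 54 for ICU stay.

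| Outcome | Current clock, active v sham | Day 90 from randomisation, active v sham |
|---|---|---|
| Reintubation | 102 − 10 = 92 v 118 − 52 = 66 (gap 26) | 90 − 10 = 80 v 90 − 52 = 38 (gap 42) |
| ICU readmission | 102 − 12 = 90 v 118 − 54 = 64 (gap 26) | 90 − 12 = 78 v 90 − 54 = 36 (gap 42) |

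The simulation assumed equal hazards in both arms of 0.4% per day for reintubation and 0.3% per day for readmission. The active arm showed more events: +0.6 to +2.4 points for reintubation and +0.5 to +1.9 for readmission under the current clock, against +1.4 to +3.0 and +1.1 to +2.4 with day 90 from randomisation.

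**The case against.** Several points on the other side stand.

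- A reader might infer that reintubation and readmission are biased in the device's favour too. The documents do not support this. Patients who leave the ICU before day 28 get about the same 90 days after discharge in either arm, and those still there at day 28 get less time at risk. The bias is neutral or against the device, and moving these outcomes to randomisation would widen the imbalance.
- The 0.8 to 3.5 points come from applying pilot medians to everyone. The trial is designed on a hazard ratio of 1.7, under which the effect is several times smaller.
- Mortality is not labelled the main safety outcome. It is one of the other secondary outcomes, outside the controlled sequence, and is also reported at hospital discharge. That second time point does not supply a common observation length, however.
- The abstract's label is shorthand. The outcome list and the visit section agree with each other, so there is no contradiction.
- A convention for never-treated participants may sit in an analysis plan that is not shown, and the article states intention to treat for the primary and key secondary outcomes, not for these. The missing starting date is a consequence of the chosen clock and no separate omission.
- It is also tempting to ask for the primary and length-of-stay clocks to start at randomisation. With first treatment due within 2 hours, that would change almost nothing.

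None of this answers the central point: followed as written, the rule gives mortality a window whose length depends on treatment.

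**Conclusion.** The concern holds for mortality only. The 90-day mortality clock starts at a date that an effective device would bring forward, so cumulative mortality is biased slightly in the device's favour. The direction follows from the stated rules if ICU discharge comes earlier in the active arm. The size rests on assumed death hazards, an assumed interval from liberation to discharge, and the effect on liberation: about 0.1 to 0.7 points at the design effect, with 0.8 to 3.5 points as an upper scenario. If the arms stop treatment at the same times, there is no bias. The primary outcome, the 150 events and the fixed testing sequence are untouched. The issue is small but cheap to remove and worth settling before the database is locked.

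**What to change.** Define mortality at day 90 from randomisation for all randomised participants. Analyse it as time to death from randomisation, censored at last contact, and label it that way in every report. This also gives never-treated participants a starting date. Keep the existing visit, the EQ-5D-5L timing and the primary clock as they are.

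Leave reintubation and readmission off this new clock. If they are compared between arms, the analysis should allow for time at risk after liberation or discharge and for death as a competing event.

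Cost: no new visit, but this redefines a protocol outcome after recruitment closed in January 2026, so it needs a documented change made while the decision-makers are still blinded. Dates of death must be recorded at the visit; the article says only that mortality is recorded. A visit may fall as early as 90 − 14 = 76 days after the last treatment, so a participant whose treatment ended before about day 90 − 76 = 14 could be censored before day 90. That may be more common in the active arm, so the extent of such censoring should be reported by arm.

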**Figure 2 F2:**
[figure not shown]
Participant timeline: schedule of enrolment, interventions and assessments. ^1^For women of childbearing potential. ^2^Participants who have no contraction of the abdominal wall muscles in response to abdominal functional electrical stimulation are not eligible for participation. ^3^To be assessed as of ICU admission. ^4^To be assessed as of ICU admission, first day of stimulation and every third day during the treatment period. ^5^Adverse Events (AEs) will be collected from the time of informed consent until hospital discharge. ^6^If any participant’s score is 4 (severe) or 5 (extreme) in any section of the survey (mobility, self-care, usual activities, pain/discomfort), the researcher will notify the PI and instruct the participant to follow up with their primary care physician for further instructions. ICU, intensive care unit; PI, principal investigator. AEs: Adverse Events, EQ-5D-5L: The 5-level EQ-5D version, SAPS III: Simplified Acute Physiology Score (SAPS) 3, SOFA: The Sequential Organ Failure Assessment.

### Follow-up visit

A follow-up visit is required 90 days (± 14 days) from the date of the final study treatment. The visit may be conducted in clinic or by phone or videoconference. The visit will record EQ-5D-5L,^36^ new hospitalisations, new intubations and mortality. If any participant’s score is 4 (severe) or 5 (extreme) in any section of the EQ-5D-5L, the research staff will notify the PI and instruct the participant to follow up with their primary care physician for further instructions.

### Sample size

Assuming an outcome expected subdistribution hazard ratio (active/sham) of 1.7, 1:1 group allocation, a type I error rate of 5% (two-sided), and 90% power, the targeted total number of participants successfully liberated from mechanical ventilation is 150. Based on the results of pilot studies, it is estimated that at least 55% of participants will achieve successful liberation. Thus, approximately 272 participants will be needed for the trial. The trial will continue to randomise participants until 150 events from the combined study groups have occurred, regardless of the total number of participants randomised. The final analysis will be performed after all randomised participants have completed or discontinued their participation in the study.

### Recruitment

All consecutive admissions will be screened against the eligibility criteria. If a patient is identified as being potentially eligible for the trial, their treating clinician will alert the study team. The study team will then approach the patient and provide them, or their LAR, with information about the trial as outlined in the Enrolment and consent section. We have estimated a recruitment period of 24 months for this trial. With the expectation of 30 sites, and a target sample size of ~272, this would require recruitment of 0.37 participants per site per month.

### Sequence generation

Participants will be considered enrolled in the study once they or their LAR have signed the informed consent form, passed the screening eligibility test, met all eligibility criteria for the study and are randomised to a treatment assignment. A web-based electronic database capture (EDC) system will be used to randomly assign participants in a 1:1 ratio to active or a sham treatment. Randomisation will be stratified by country, with varying block sizes. Prior to trial initiation, an independent statistician who is not involved in the clinical aspects of the trial will generate the randomisation schedule. Randomisation will be requested by a suitably qualified local investigator for each participant. Randomisation sequences will be concealed within the EDC, with only an independent statistician having access to the allocation schedule.

